#### *Secondary outcomes*

##### 

**Detection** Differences in proportions of women in the control and intervention group scoring 13 or more on the EPDS, and categorized as some or high-risk on the ALPHA will be estimated using chi-square tests.

##### 

**Disclosure** Comparison of mean scores of the subscales of the DES (risk, benefit of disclosure) will be done using two-tailed independent sample t-tests.

##### 

**Factors associated with acceptability, feasibility, and disclosure** We will use multivariable logistic regression to determine predictors of acceptability, feasibility, and disclosure and report relative risks and 95% CIs. Outcomes will be dichomotized measures of acceptability, feasibility (based on CAE), and disclosure (based on DES) where ‘high’ acceptability, feasibility, and disclosure will include participants whose responses place them above the 75th percentile for the measure. Models will be built using variables that are associated with outcomes at *P* <0.10 on crude analyses, entering demographic variables in a first block, followed by obstetrical factors, mental health history, and the ACES score. Results will be reported as odds ratios and 95% CIs.

##### 

**Psychometric properties** Psychometric properties of internal consistency (Cronbach’s alpha; item-total correlation) will be calculated for the EPDS by modality. Predictive validity measures of sensitivity, specificity, positive predictive value, and negative predictive value will be calculated using clinical interview diagnosis as the reference. Comparisons of the psychometrics between the two modalities will be made by correlational analysis using Cohen’s guidelines [59]. In terms of further tool development of the ALPHA, we will develop an integer score-based prediction rule for the prevalence of anxiety and depression, according to MINI diagnosis. This method was previously used to develop a prenatal screening tool for postpartum distress by two members of the research team (SM, DK) [60]. We will develop a best fit multiple regression model predicting depression and/or anxiety as per clinical interview diagnosis, candidate variables for which will be drawn from the ALPHA. A regression coefficient-based scoring algorithm [60] will be applied to the final regression model in order to develop a single screening score. Receiver operating characteristic (ROC) analysis will then be used to determine an optimal cutoff for the screening score. Finally, we will perform a ROC analysis for each modality (e-version *versus* paper-based) and compare indices of sensitivity, specificity, positive and negative predictive values using Cohen’s guidelines [60]. All analyses will be conducted in the total sample, with subgroup analyses conducted by medical risk to determine whether the scoring is robust across risk subgroups.

##### 

**Cost-effectiveness** For the economic analysis, we will estimate the incremental costs-effectiveness (ICER) for the e-screening alternative compared to the paper-based alternative. The e-screening costs include investment costs to technology (programs, tablets, data storage) and the operating costs at the clinic that may differ somewhat from the conventional group administrative and analytical cost. Cost-effectiveness is determined by incremental cost to identify a woman with increased risk of prenatal and postpartum depression and anxiety. Because we are not going to follow up the screened women, the costs and outcomes after the screening are not included in this initial economic analysis.

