There is a clear need for a rigorous evaluation of the feasibility, acceptability, and psychometric performance of e-screening for prenatal mental health difficulties. A key consideration for evaluation is to determine whether established assessment tools are valid and reliable for use when delivered online. For example, it has been shown that some tools have different psychometric properties when delivered online, suggesting a need for different cutoff points [44]. Another key issue is the inclusion of women experiencing a broad range of degrees of psychosocial risk. Pregnant women with high-risk pregnancies represent a vulnerable group in that the prevalence of mental health problems in this group is more than three times greater than medically low-risk women [45,46]; however, medically high-risk women are rarely included in intervention studies of perinatal mental health.

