1. To compare the level of detection of symptoms of prenatal depression, anxiety, and psychosocial risk in e-screening *versus* paper-based screening	Compared to paper-based screening, what is the effect of mental health e-screening in pregnant women on the detection of prenatal depression, anxiety, and psychosocial risk?	Proportion of women scoring above cutoff point of EPDS for depression and anxiety; proportion of women identified as some or high psychosocial risk on ALPHA	EPDS	Compared to the control group, a higher proportion of women in the intervention group will: (1) score 13 or more on the total EPDS (corresponding to probable prenatal depression); (2) score 4 or more on the anxiety subscale of the EPDS (Q3, 4, 5) (corresponding to probable prenatal anxiety); and (3) be identified as having some/moderate or high psychosocial risk on the ALPHA
			ALPHA	
2. To compare the level of disclosure of symptoms of prenatal depression and anxiety, and psychosocial risk in e-screening *versus* paper-based screening	Compared to paper-based screening, what is the effect of mental health e-screening in pregnant women on the disclosure of prenatal depression, anxiety, and psychosocial risk?	Level of disclosure: Mean subscale scores: (1) risk of disclosure; (2) benefits of disclosure	DES	Compared to paper-based screening, e-screening promotes greater disclosure (for example, the mean score risk of disclosure is significantly lower and benefit of disclosure is significantly higher in the e-screening group)
3. To determine factors associated with the acceptability and feasibility of mental health e-screening as well as disclosure	What factors are associated with acceptability and feasibility of mental health e-screening in pregnant women?	Identification of factors that significantly increase odds of acceptability and feasibility of e-screening	Quantitative: (1) Demographic variables (age, gestation, marital status; ethnicity); (2) mental health history; current mental health status; EPDS scores; ALPHA category; (3) DES scores; (4) medical risk; (5) features of the screening instrument/process	Factors that are significantly associated with acceptability and feasibility: mental health history, current mental health status (EPDS, ALPHA), disclosure (DES), medical risk; features of screening instrument
			Qualitative:	
			Semi-structured interviews	
				Factors not associated: demographics

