4. To compare the psychometric properties (sensitivity, specificity, cutoff points) of paper-based ALPHA and EPDS *versus* the e-version administered to medically low- and high-risk pregnant women	Are the psychometric properties (for example, sensitivity, specificity, cutoff points) similar or better in the ALPHA and EPDS e-version compared to the paper-version when administered to pregnant women?	Psychometric properties: sensitivity, specificity of ALPHA and EPDS in paper-based and e-versions	ALPHA, EPDS, MINI	The psychometric properties of e-version of ALPHA and EPDS are similar or better compared to paper-based version
5. To compare the cost-effectiveness e-screening compared to paper-based screening	Is e-screening as a component of routine prenatal care cost effective when compared to paper-based screening?	Cost-effectiveness: actual costs	The expected incremental cost effectiveness of e-screening is cost effective at values of health considered acceptable in the Canadian healthcare system	E-screening will be cost effective

ALPHA: Antenatal Psychosocial Health Assessment; CAE: CASI Assessment Evaluation; DES: Disclosure Expectations Scale; EPDS: Edinburgh Postnatal Depression Scale; MINI: Mini International Neuropsychiatric Interview.

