#### *The intervention*

The intervention is psychosocial assessment via electronic administration. Women assigned to the intervention group will complete the psychosocial assessment comprising the ALPHA and the EPDS electronically using a computer tablet. Rather than the traditional, sole use of symptom-based mental health screening tools, the combined use of a psychosocial risk assessment instrument (for example, ALPHA) that detects current and future risk for mental health problems and a symptom screening tool (for example, EPDS) that detects current symptomatology has been recommended as the most effective, comprehensive approach to psychosocial assessment [3].

The ALPHA was selected for use as a psychosocial risk assessment tool because its paper-based version is currently used in our clinic recruitment sites. In addition, the ALPHA is a Canadian-developed tool that has been tested in the Canadian context in primary care [13,30] and has been gaining popularity for antenatal psychosocial assessment in these settings. It was designed to identify psychosocial risk factors in pregnant women that may increase their risk for adverse psychosocial outcomes (for example, stressful life events, lack of support), including postpartum depression [50,51]. It has undergone extensive face and content validity by experts including obstetricians, family physicians, and midwives [30], and identifies significantly more cases of psychosocial risk than non-standardized assessment [51]. The majority of providers indicated that the tool could readily be implemented in routine prenatal care and pregnant women found it acceptable [33]. The self-report version used in this study is easily completed in 5 to 10 minutes. It asks women questions on the topics of family life, stressors, feelings about the pregnancy, substance use, abuse, and family of origin. Women respond with yes/no or 6-point Likert-scale options. Based on a review of responses in each category, trained providers subjectively judge whether women are at low, some, or high psychosocial risk. No cutoff points or scoring algorithm have been developed and thus sensitivity and specificity data are not available. Risk categories are then used to create a care plan.

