### Secondary outcomes

The five secondary outcomes are (see measures in Table 1b):

(1) the proportion of pregnant women scoring 13 or more on the total EPDS, 4 or more on the anxiety subscale, and identified as some or high psychosocial risk on the ALPHA;

(2) the level of disclosure as assessed by mean scores on the Perceived Risk and Perceived Utility subscales of the Disclosure Expectations Scale (DES) [55]. The DES is an 8-item scale designed for evaluation of the perceived risk (items 1, 2, 4, and 5) and benefit (items 3, 6, 7, and 8) of disclosure. Convergent validity of the subscales has been demonstrated with other measures of self-disclosure, as well as psychological distress, and intention to seek mental healthcare [55];

(3) description of factors that significantly increase the odds of acceptability, feasibility, and disclosure related to each form of screening;

(4) psychometric properties (for example, Cronbach’s alpha, sensitivity, specificity, positive and negative predictive values) of the e-version of the EPDS and ALPHA. A scoring algorithm does not currently exist for the ALPHA (for example, the trained provider subjectively judges risk based on responses); however, an algorithm would promote standardization in clinical decision-making and efficiency since a score could be calculated as part of e-screening. We plan further tool development comprising derivation of a quantitative scoring method for classifying women into psychosocial risk categories; and

(5) cost-effectiveness of detecting clinical depression and anxiety in e-screening *versus* usual screening (that is, equipment and human resource costs of e-screening *versus* paper-based - see Secondary outcomes).

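### The EPDS detection test counts screen-positives at one cutoff in both modes, so lost specificity on the tablet could pass as better detection; the cost-effectiveness effect is defined inconsistently

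*Protocol article*

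**What the plan says.** **Detection.** Table 1b, secondary objective 1, hypothesises: "Compared to the control group, a higher proportion of women in the intervention group will: (1) score 13 or more on the total EPDS", with parallel statements for 4 or more on the anxiety subscale and for some or high risk on the ALPHA. The Detection paragraph of the Analysis compares "Differences in proportions of women in the control and intervention group scoring 13 or more on the EPDS", together with the ALPHA categories, by chi-square test. It does not mention the anxiety subscale, which Table 1b and the Secondary outcomes list both include. The ALPHA category is a provider's judgement: "No cutoff points or scoring algorithm have been developed".

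**The reference standard.** Under Confirmation of diagnosis, all women are to have a MINI within 1 week from a blinded interviewer. The Psychometric properties paragraph uses it for sensitivity, specificity and predictive values, compared between modes.

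**Cutoffs online.** The Background notes that "some tools have different psychometric properties when delivered online, suggesting a need for different cutoff points".

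**Cost-effectiveness.** The Secondary outcomes list describes "cost-effectiveness of detecting clinical depression and anxiety in e-screening". The Analysis says: "Cost-effectiveness is determined by incremental cost to identify a woman with increased risk of prenatal and postpartum depression and anxiety", and adds that "the costs and outcomes after the screening are not included in this initial economic analysis". Table 1b, secondary objective 5, has the entry: "The expected incremental cost effectiveness of e-screening is cost effective at values of health considered acceptable in the Canadian healthcare system".

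**The concern.** Randomization makes the true prevalence of depression and anxiety equal between arms in expectation. It does not say where a surplus of screen-positives on the tablet comes from. The surplus may be true cases who disclosed more readily, or it may be a mode effect that moves women without a disorder over the cutoff. The detection test cannot separate the two, and the hypothesis reads both as benefit.

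The cost-effectiveness analysis has a related weakness. If its effect is women at increased risk, additional false positives could enlarge the denominator, and because costs after screening are excluded, following them up would cost nothing in the ratio. If its effect is clinical depression and anxiety, neither holds in the same way. The text does not settle which is meant.

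At stake is a conclusion that e-screening detects more depression, and does so at acceptable cost, when it may have found no additional case.

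**Working it through.** **1. The plan's own figure.** n = 0.85 × 0.15 × (1.96/0.05)² = 195.9, so 196; 196/(1 − 0.25) = 261.3, stated as 261 per group. This reproduces. It was set for the precision of a single proportion, not for the detection comparison; it is used below only as the arm size.

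**2. Inputs.**
- EPDS sensitivity 0.85 and specificity 0.77 (The intervention).
- Prevalence p from 0.13 to 0.29 (Introduction).
- Two-sided 0.05 (the Analysis sets 0.05 for all analyses; two-sided is assumed for the chi-square test).
- Assumed, not in the documents: tablet specificity lower by d = 0.05, 0.10 or 0.15, with sensitivity unchanged.

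**3. Formulas.**
- Screen-positive rate, paper: P = 0.85p + 0.23(1 − p).
- Screen-positive rate, tablet: T = 0.85p + (0.23 + d)(1 − p).
- True-positive rate, both modes: 0.85p. Positive predictive value on paper: 0.85p/P.
- Chance that the test favours the tablet: Φ[((T − P) − 1.96·SE0)/SE1], with SE0 the pooled and SE1 the unpooled standard error.

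**4. On paper.** At p = 0.13, P = 0.1105 + 0.2001 = 0.311 and the positive predictive value is 0.1105/0.3106 = 0.356. At p = 0.29, P = 0.2465 + 0.1633 = 0.410 and the value is 0.2465/0.4098 = 0.602. So 31% to 41% screen positive, and 36% to 60% of those are cases.

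**5. A 10-point loss, worked.** At p = 0.13, T = 0.1105 + 0.33 × 0.87 = 0.398, a difference of 0.087. SE0 = 0.0419 and SE1 = 0.0417, so (0.087 − 0.0821)/0.0417 = 0.12 and the chance is 55%. At p = 0.29, T = 0.481 and the difference is 0.071. SE0 = 0.0435 and SE1 = 0.0434, so (0.071 − 0.0853)/0.0434 = −0.33 and the chance is 37%.

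**6. Range at 261 per arm.**

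| Assumed specificity loss | p = 0.13 | p = 0.29 |
|---|---|---|
| 5 points | 18% | 13% |
| 10 points | 55% | 37% |
| 15 points | 87% | 69% |

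At 196 per arm, the 10-point row becomes 44% and 29%.

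**7. Higher prevalence.** At an illustrative p = 0.40, P = 0.340 + 0.138 = 0.478 and T = 0.340 + 0.198 = 0.538. The positive predictive value on paper is 0.340/0.478 = 71%, and the chance for a 10-point loss falls to about 28%.

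**8. A MINI-confirmed endpoint in the same scenarios.** The rate is 0.85p in both arms, so the expected difference is zero. With a 10-point loss, the planned endpoint adds 261 × 0.087 = 23 women at p = 0.13, or 261 × 0.071 = 19 at p = 0.29, none of them a confirmed case.

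**9. The cost-effectiveness statements side by side.** The Secondary outcomes list counts clinical disorder, the Analysis counts increased risk, and Table 1b refers to values of health. The first two are different denominators. The third needs a health outcome, and outcomes after screening are excluded, so it cannot be assessed with the data described.

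**The case against.** The strongest reply is that the safeguard is already planned. Sensitivity, specificity and predictive values against the MINI will be reported by mode, and the remark about online cutoffs is the stated reason for evaluating validity. A 10-point specificity loss would be visible there. This stands, and it would be wrong to infer that the MINI goes unused or that false positives would be hidden. It does not resolve the point. The accuracy results form a separate secondary outcome, nothing makes the detection conclusion depend on them, and the comparison named for them, a correlational analysis by Cohen's guidelines, is not a test of whether specificity differs between two independent groups.

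It can also be said that the objective concerns symptoms and risk, with 13 or more denoting probable depression, so screen-positive yield is a legitimate outcome. That is fair as grounds for keeping the yield, but not for reading a higher yield as better detection.

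The size depends on assumptions. No specificity loss is given in the documents, and the Background cites a small study of Internet-based postpartum depression screening tools, the EPDS among them, with excellent validity. The 13–29% prevalence covers depression and anxiety in pregnancy and postpartum, not MINI-diagnosed depression. The quoted predictive value of 83%, taken with 85% and 77%, implies a prevalence of about 57%, so those accuracy figures come from a different case mix. With about 45 of 95 monthly candidates on the high-risk unit (Feasibility of achieving sample size), prevalence may exceed 29%, which lowers the chance.

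Three stronger readings are not supported. No passage says that the cost-effectiveness ratio counts screen-positives at a fixed cutoff. The fixed cutoff does not apply to the ALPHA. And one cannot infer that more women without illness would be referred throughout: at the clinics referral follows the nurse's judgement of risk, only the hospital procedure names the EPDS cutoff, and a MINI-negative woman above it still reports symptoms.

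**Conclusion.** The point holds for the EPDS detection test. As written, a specificity loss online could be declared better detection with no additional true case. Under the stated accuracy and prevalence the chance is modest for a 5-point loss, substantial for 10 points and high for 15, and smaller throughout at higher prevalence. These figures are conditional on an assumed loss with unchanged sensitivity; they do not predict that the loss will occur. Separately, and without any assumption, the effect in the cost-effectiveness ratio is described in three ways that cannot all be used, one of which cannot be assessed from the data planned. Both matters concern secondary outcomes, and the planned accuracy analysis gives partial protection, so this should be fixed rather than must be fixed.

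**What to change.** - **Detection claim.** For the EPDS total (13 or more, with a MINI depressive disorder) and the anxiety subscale (4 or more, with a MINI anxiety disorder), base any claim of better detection on women who are screen-positive and MINI-positive per woman randomized. Give the between-arm difference with a 95% CI, and report the proportion screen-positive but MINI-negative beside it. Name the anxiety subscale in the Detection paragraph.
- **Yield.** Keep the raw screen-positive share, labelled as yield. Keep ALPHA risk as a descriptive yield outcome, because it has no MINI counterpart.
- **Cost-effectiveness.** Use MINI-confirmed cases detected as the effect in Table 1b, the Secondary outcomes list and the Analysis. Show the result over a range of willingness to pay per case; this also copes with a difference in cases near zero, where the ratio itself is undefined. Drop the test against values of health.

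The cost is wording and analysis only, since the MINI is already planned for all women. The downsides are fewer events, hence less power for detection, and the need for a missing-data rule for women without a MINI; the sample size section allows for 25% attrition. The sample size is unaffected, as it was not set on detection.

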#### Sample size

##### 

**Determination of sample size** Because no data are available to guide estimation of a minimal clinically important difference in ‘true’ cases detected through e-screening a ‘confidence interval (CI) approach’ [56] was used. Based on high levels of acceptability and disclosure reported using computer screening [39,40], e-screening would be feasible if, in the intervention group: (1) 85% of women indicated that they were able to tell the truth on all items (Q7 CAE); (2) 85% scored 4 to 8 on the Risk subscale of the DES (no/slight perceived risk to disclosure); and (3) 85% scored 16 to 20 on the DES Utility subscale (for example, disclosure moderately or very beneficial). The sample size calculation (Table 2) indicates that 261 women per group (*n* = 522) is required.

**Table 2 T2:** Sample size determination

**Using the calculation of a confidence interval for a proportion, a 95% CI and a margin of error of 0.05:**	**Accounting for an estimated attrition/loss to follow-up of 25% based on other reported rates in pregnant and postpartum women (55,66):**
p = a priori estimate of % of interest; *n* = sample size	*n* = total sample size; L = attrition rate + loss-to-follow up
*n* = p(1-p) [1.96/.05]^2^	N_new_ = n/(1-L)
*n* = 0.85(1–0.85) [39.2]^2^	N_new_ = 196/(1–0.25)
*n* = 196	N_new_ =261

Therefore a minimum of 261 women per group would be required.

##### 

**Feasibility of achieving sample size** The maternity clinics conduct initial prenatal visits for a total of 50 women per month across all clinics. The number of new patients on the high-risk antenatal unit is similar at 45 women per month. Clinic staff estimates that roughly 4% of women would be ineligible due to language (96% eligible = 91 women per month). A conservative estimation of 50% participation rate [57,58] would yield 46 women per month. Thus, recruitment of women is expected to take 12 months.

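### The objective-3 regression promises two different effect measures, leaves most of its hypothesised factors and study arm out of the named blocks, and fixes no direction for a DES whose subscales oppose each other

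*Protocol article*

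**What the plan says.** All of this is in the protocol article. Under Analysis, Secondary outcomes, the paragraph on factors associated with acceptability, feasibility and disclosure specifies multivariable logistic regression on dichotomised outcomes.

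- **Outcome.** The group coded as high is defined by one rule: "acceptability, feasibility, and disclosure will include participants whose responses place them above the 75th percentile for the measure". The CAE supplies the feasibility outcome and the DES the disclosure outcome. No DES subscale and no scoring direction are given.
- **Effect measure.** The models will "report relative risks and 95% CIs". The paragraph closes with "Results will be reported as odds ratios and 95% CIs".
- **Covariates.** Variables associated at P<0.10 in crude analyses are carried forward, "entering demographic variables in a first block, followed by obstetrical factors, mental health history, and the ACES score".

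Elsewhere:

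- **Table 1b, objective 3** expects association with "mental health history, current mental health status (EPDS, ALPHA), disclosure (DES), medical risk" and features of the screening instrument, and no association with demographics.
- **Table 1b, objective 2** describes greater disclosure as the case where "the mean score risk of disclosure is significantly lower and benefit of disclosure is significantly higher in the e-screening group".
- **Sample size** treats a low Risk score as favourable ("85% scored 4 to 8 on the Risk subscale of the DES (no/slight perceived risk to disclosure") and a Utility score of 16 to 20 as favourable.
- **The list of secondary outcomes** speaks of factors that raise the odds of each outcome for each form of screening.

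**The concern.** An analyst who follows this paragraph has to make three choices that the text either contradicts or leaves open, and each one changes what is estimated.

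A reader who sees a reported value of 2 cannot interpret it without knowing whether it is a relative risk or an odds ratio, because the outcome is not rare. A multivariable model restricted to the named blocks adjusts for demographics and history, but does not contain most of the factors that the objective was written to examine. It also has no term for arm. Under Outcomes and measurement, intervention women rate e-screening they have experienced, while control women answer adapted CAE questions about e-screening they have not used. A pooled model without arm therefore mixes two different questions in one outcome. Finally, a single rule based on being above a percentile cannot suit both DES subscales when they point in opposite directions.

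**Working it through.** **1. The plan's own figure.** The only calculation that uses the DES cut-offs is the sample size: 0.85 × 0.15 × (1.96/0.05)² = 195.9, so 196. Then 196/(1 − 0.25) = 261.3, stated as 261, and 2 × 261 = 522. It reproduces, and nothing below changes it.

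**2. Relative risk against odds ratio.** A cut above the 75th percentile codes at most 25% of the modelled women as high. Two assumptions bracket the conversion.

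*25% in the reference group*, OR = [p1/(1 − p1)] / [p0/(1 − p0)]:
- RR 1.5: p1 = 0.375, OR = (0.375/0.625)/(0.25/0.75) = 1.80
- RR 2.0: p1 = 0.50, OR = (0.50/0.50)/(0.25/0.75) = 3.0

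*25% overall in two equal groups*, p0 = 0.50/(1 + RR):
- RR 1.5: p0 = 0.20, p1 = 0.30, OR = (0.30/0.70)/(0.20/0.80) = 1.71
- RR 2.0: p0 = 0.167, p1 = 0.333, OR = 0.50/0.20 = 2.5

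The other way round, RR = OR/(1 − p0 + p0 × OR). At p0 = 0.25, odds ratios of 1.5, 2 and 3 are relative risks of 1.33, 1.60 and 2.00. At p0 = 0.15 they are 1.40, 1.74 and 2.31. Ties on a short integer scale can push the share coded high below 25%. The gap then narrows but does not close.

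**3. Hypothesised factors against named blocks.**

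| Table 1b, objective 3 | Block in the analysis paragraph |
|---|---|
| Mental health history | Yes |
| Current mental health status (EPDS, ALPHA) | None |
| Disclosure (DES) | None |
| Medical risk | Not named; could fall under obstetrical factors |
| Features of the screening instrument | None |
| Demographics (expected not associated) | Yes, first block |

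ACES has a block but no place in the hypothesis. Study arm appears in neither list.

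**4. Direction of the DES rule.** The outcome could be Utility, reversed Risk, unreversed Risk or an unreversed total.

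- On Utility or reversed Risk, a high score means greater disclosure and the rule works.
- On an unreversed total, opposing items are added together.
- On unreversed Risk, suppose the planning value holds in the modelled sample, so that 85% score 4 to 8 and 15% score higher. The 75th percentile is then at most 8. The group above it contains all 15% who score above 8 and at most 25% − 15% = 10% with no or slight perceived risk. At least 15/25 = 60% of the women coded as high disclosure would be those who perceive the most risk.

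**5. Percentile against fixed thresholds.** If 85% of the modelled women score 16 to 20 on Utility and at most 25% lie above the 75th percentile, at least 85% − 25% = 60% meet the plan's favourable range but are coded not high. Three assumed integer score shapes give 68% to 85%. In the top-heavy one the 75th percentile is the maximum score of 20 and nobody is coded high. The protocol gives no score distribution, so these shapes are illustrations only.

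**The case against.** **The intended effect measure can be recovered.** The logistic model, the closing sentence of the paragraph, the list of secondary outcomes and Table 1b all point to odds, and relative risks are mentioned once. This supports odds ratios as the correction. It does not remove the contradiction within one paragraph, and the difference is material at this prevalence.

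**The hypothesis is not wholly untested.** A reader might infer that it cannot be tested at all. That goes too far. Each factor in Table 1b can be examined at the crude step, mental health history and demographics have blocks, and medical risk may be covered by obstetrical factors. What stands is narrower: EPDS, ALPHA, DES and screening features have no stated place in the multivariable model. Arm-specific models would resolve the missing arm term and would fit the reference to each form of screening, but none are stated.

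**Inversion is not stated.** A reader might infer that the plan definitely labels the most risk-averse women as high disclosers. It names no subscale, and Table 1b and the sample-size section show that the authors know low Risk is favourable. The inversion follows only if the rule is applied to unreversed Risk.

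**The 85% criteria serve another purpose.** A reader might also infer that the percentile rule contradicts them. Those criteria are set for the intervention group, to define feasibility and size the trial, while the percentile defines a secondary regression outcome. This is a mismatch of definition. The 60% in step 5 also carries the intervention-arm figure over to all women. If, for illustration, 60% of controls were in the favourable range, the pooled figure would be (85% + 60%)/2 = 72.5% and the bound would fall to 47.5%.

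**Conclusion.** The point holds in three parts, of moderate severity. The conflict between relative risks and odds ratios is unconditional. Its size rests on an outcome of about 25%, where a relative risk of 2.0 is an odds ratio of 2.5 to 3.0. The gap between the named blocks and Table 1b also follows directly from the text: most of the objective-3 hypothesis, and study arm, have no stated place in the multivariable model. The DES direction is conditional. The rule is badly fixed for an instrument with opposing subscales, and it reverses the meaning of the outcome only if unreversed Risk is used.

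The quartile cut sits poorly with the planning values for the DES, but that is a reason to prefer another coding and not an error in itself. Only secondary objective 3 is affected. The primary analysis, the sample size and the data collected are not.

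**What to change.** Rewrite the one paragraph, before these models are fitted, as follows.

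1. Report odds ratios only, in line with Table 1b and the list of secondary outcomes. If relative risks are wanted, name a model that estimates them, such as modified Poisson regression.
2. Enter the Table 1b factors (EPDS, ALPHA, medical risk, screening features, and DES where it is not the outcome) and study arm, or fit the models separately by arm.
3. State which DES subscale defines disclosure, and reverse Risk so that a high value always means greater disclosure.
4. Preferably, model the DES and CAE scores as continuous instead of cutting at a sample percentile. The effect measure for those outcomes is then a difference in score, and the references to odds should be adjusted to match.

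Arm-by-factor interaction terms are optional. Reducing feasibility to a single CAE item is not needed.

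The cost is wording only. The questionnaires are already administered to both groups, so no new data are required and the sample size does not change.
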